3. BMI
4. Diabetes
5. Pulmonal disease
6. Smoking/no smoking
7. Hernia occurrence/operation prior to prostatectomy.
8. Physical activity

9. Preoperative tumour risk category defined as follows:

**Low risk T1-2 vs high risk T3-4**

**BASELINE PATIENT CHARACTERISTICS, TUMOUR FACTORS, COMORBIDITIES AND RISK FACTORS ARE BASED UPON:**

### **Preoperative questionnaire**

Sociodemographics (Q4-6), BMI (Q8-9), relevant comorbidities (Q30, 35, 41, 43, 44), previous abdominal surgery (Q52), previous IH surgery (Q46, 47), smoking (Q57), physical activity (Q143), urinary flow (Q149)

Patients were dichotomized as current smoker (including pipe smoking) or non-smoker (former smoker or never smoker) according to their answer to the question “Do you smoke or have you smoked?”.

Q 143: Hur ofta har Du varit fysiskt aktivt i 30 minuter eller mer den senaste månaden..? *With a 4 point Likert scale (1= aldrig, 2=ibland (1-2 ggr/v), 3=Ofta (3-4 ggr/v), 4= Dagligen eller nästan dagligen (5-7 ggr/vecka)) The answers will be dichotomized with a cut-off point between 2 and 3 prior to analysis.*

Q 146: Hur ofta har Du varit tvungen att trycka på eller krysta för att börja kissa den senaste månaden? *With a 6 point Likert scale (1=aldrig, 2=färre än 1 av 5 vattenkastningar, 3=färre än hälften av vattenkastningar, 4= ungefär hälften av vattenkastningar, 5= fler än hälften av vattenkastningar, 6=alltid). The answers will be dichotomized with a cut-off point between 3 and 4 prior to analysis.*

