### **CRF preoperatively**

Item 6, clinical stage (cT1-T4)

Item 8, ASA-classification

Item 9, PSA

Item 20, biopsy Gleason score

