## ***Covariates, stratum and subgroups***

No additional variables apart from the variables that will be evaluated for risk factors will be included as covariates in the statistical model.

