## ***Key Secondary objective***

A second object is to analyse the primary variable with the same possible risk factors as above, but include Lymph node dissection in the model.

Item 31-33 Lymph node dissection:,yes vs no

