#### **Statistical method**

The primary objective of evaluating the association between hernia incidence and operation and the evaluation of risk factor will be done simultaneously with the same statistical model. The relative risk of at least one inguinal hernia within 24 months after surgery, comparing surgical methods (RALP, RRP), will be modelled using a modified Poisson regression approach of Zou ([10]).

Except for the exposure, the surgical method (RALP, RRP), possible risk factors (age, physical workload, BMI, diabetes, pulmonary disease, smoking, hernia prior operation, physical activity and tumour size) will be evaluated by the same algorithm introduced by Bursac ("Purposeful selection of variables in logistic regression", Source Code for Biology and Medicine 2008;17). This model might also include interactions.

The key secondary objective will evaluate the same risk factors, but will include Lymph node dissection (yes/no) in the model.

The secondary objectives will be evaluated in an analogous way, using the risk factors ....

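### The preoperative tumour risk covariate uses clinical T stage alone although PSA and biopsy Gleason are recorded, so residual confounding by tumour risk is possible in the RALP versus RRP and lymph node dissection estimates

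*SAP*

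**What the plan says.** Item 9 of the risk-factor list (SAP, Variables and Endpoints) is introduced as "Preoperative tumour risk category defined as follows", and the definition is "Low risk T1-2 vs high risk T3-4". The T stage comes from the preoperative CRF, "Item 6, clinical stage (cT1-T4"). The same CRF list also contains PSA (Item 9) and "Item 20, biopsy Gleason score". Neither appears again in the SAP.

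The section on covariates, stratum and subgroups closes the list: "No additional variables apart from the variables that will be evaluated for risk factors will be included as covariates in the statistical model". The key secondary objective keeps the same risk factors and says it will "include Lymph node dissection in the model".

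The variable has three names. It is a tumour risk category in the risk-factor list, and tumour stage (low and high risk) under Demography and patient characteristics. Under Statistical method the candidate list ends "hernia prior operation, physical activity and tumour size) will be evaluated by the same algorithm", that is, purposeful selection. No tumour size measurement is listed anywhere.

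The Analysis population section states that the study is non-randomised and analysed as treated.

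**The concern.** Without randomisation, the technique risk ratio depends on covariate adjustment, and this binary is the only tumour covariate. By construction, a man with cT1-2 disease is coded low risk whatever his PSA and Gleason score. If those markers influenced which operation he had, or whether nodes were dissected, and are also related to hernia (directly or through the extent of surgery), a T-stage split would adjust for tumour risk only in part.

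Two further features of the plan add to this. PSA and Gleason are absent from the descriptive list, so the planned characteristics table would not show an imbalance between RALP and RRP. And because the tumour term goes through purposeful selection, even the T-stage adjustment could drop out.

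**Working it through.** **1. The SAP's own figures.** Sample size gives 2764 RALP and 942 RRP men, and power of about 35% at 6% vs 7.5% and 55% at 10% vs 12.5% (two-sided 5%). A two-proportion normal approximation with continuity correction:

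power = Φ{ [|p1 − p2| − ½(1/n1 + 1/n2) − 1.96·SE_pooled] / SE_unpooled }

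- 6% vs 7.5%: (0.01429 − 0.01807)/0.00970 = −0.39, power 34.8%.
- 10% vs 12.5%: (0.02429 − 0.02280)/0.01219 = 0.12, power 54.9%.

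Both figures reproduce. They do not depend on the tumour covariate, and no arithmetic error is claimed.

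**2. What the SAP supplies on confounding.** Bias requires two things: PSA or Gleason must differ between RALP and RRP within T-stage group, and must predict hernia given technique and the other covariates. The SAP gives no distribution of either marker by group, no association with hernia, and no rule for who has lymph nodes dissected. The size of any bias cannot be derived from it.

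**3. Illustration under stated assumptions.** Take men coded T1-2. Let q be the share with high PSA or Gleason in each surgical group, and R the hernia risk ratio for such men. Assume no other covariate captures the difference. The factor by which the RALP:RRP risk ratio is multiplied is

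B = [1 + q_RALP(R − 1)] / [1 + q_RRP(R − 1)].

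All values of q and R below are assumed.

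| q_RRP vs q_RALP | R = 1.0 | R = 1.2 | R = 1.5 | R = 2.0 |
|---|---|---|---|---|
| 15% vs 10% | 1.00 | 0.990 | 0.977 | 0.957 |
| 20% vs 10% | 1.00 | 0.981 | 0.955 | 0.917 |
| 30% vs 15% | 1.00 | 0.972 | 0.935 | 0.885 |
| 30% vs 10% | 1.00 | 0.962 | 0.913 | 0.846 |

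Example, last cell: (1 + 0.10)/(1 + 0.30) = 0.846.

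A true risk ratio of 0.80 would be read as 0.80 at R = 1.0, 0.77 to 0.79 at R = 1.2, 0.73 to 0.78 at R = 1.5, and 0.68 to 0.77 at R = 2.0.

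**4. Sensitivity to the assumptions.** If the remaining imbalance is only 10% vs 5% (RRP vs RALP), B is 1.015/1.03 = 0.985 at R = 1.3 and 1.05/1.10 = 0.955 at R = 2.0. If the imbalance runs the other way (RALP 30%, RRP 10%), B at R = 2.0 is 1.30/1.10 = 1.18, so a true 0.80 would move towards 1.

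**5. Lymph node dissection.** The same formula applies with shares in dissected and undissected men, but the SAP offers no basis even for choosing a range, so no figure is given.

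**The case against.** The strongest reply is that the SAP fixes an explicit, reproducible definition, says under Interpretation of results that its variables rest on clinical judgement and earlier studies, and promises cautious interpretation. The outcome is hernia, not a cancer outcome. Local tumour extent may be what matters, and the name tumour stage agrees with a T-stage cut. That is a fair reading. If it is what was meant, the label *risk category* is too broad and the SAP should say so.

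A reader might go further than the SAP allows in four ways:

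- **That confounding is present, or that most selection on PSA and Gleason goes unadjusted.** The SAP shows neither an imbalance within T stage nor a link between these markers and hernia. Confounding is possible, not demonstrated.
- **That the lymph node estimate is affected more than the technique estimate.** This would need dissection to have been decided on these markers, which the SAP does not state. Any effect of tumour risk that acts through dissection is part of the dissection effect, not confounding of it.
- **That the shift should be judged against a planned effect of 0.80.** The SAP says the sample size was not calculated for hernia. The 0.80 is a previous study's result used to illustrate power.
- **That high-risk men are misclassified against a recognised grouping.** The SAP contains no such grouping. All that follows is that PSA and Gleason do not affect the coding.

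It is also fair to say that redefining the variable alone would not secure the adjustment, because selection could remove the new term as readily as the old one. The fix has to address this.

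**Conclusion.** The point holds as a matter of prespecification. A covariate labelled as tumour risk uses one of three recorded preoperative markers, the covariate rule excludes the other two, and the variable has three names, one of which (size) corresponds to no listed measurement. Residual confounding by tumour risk is therefore possible in both the primary and the key secondary model.

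Its size is not known. Under the assumed imbalances it runs from no effect, if tumour risk does not affect hernia, to a shift in the risk ratio of roughly 10 to 15% in the stronger scenarios (R = 2.0 with 30% of RRP men affected against 10 to 15% of RALP men). With smaller imbalances or weaker effects it is only a few per cent. The direction depends on which group carries more high-risk disease. The naming inconsistency needs correcting whatever the size of the bias.

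**What to change.** In the primary and key secondary models, enter cT stage, log PSA and biopsy Gleason group as prespecified adjustment terms, or one category derived from all three with its cut points written in the SAP. State that these terms stay in the model whatever purposeful selection decides. Amend the covariates section and the variable list under Statistical method to match. Report PSA and Gleason by surgical group in Table 1. Use one name for the variable in the risk-factor list, the demography list and the statistical method, and remove the reference to tumour size.

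If the sponsor intends T stage as a marker of local extent, the SAP should rename the variable accordingly and add the three-marker model as a prespecified sensitivity analysis.

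The cost is small. The data are on the preoperative CRF, and the planned multiple imputation of risk factors would cover missing values. The SAP's illustrative incidences imply about 0.06 × 2764 + 0.075 × 942 = 236 to 0.10 × 2764 + 0.125 × 942 = 394 men with hernia, enough for a few extra parameters. The downside is slightly wider intervals if the markers turn out not to predict hernia.

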### **Questionnaire three months:**

Q 8: Har ditt arbete varit kroppsligt aktivt den senaste månaden? *With a 6 point Likert scale (0=Inte aktuellt jag jobbar inte, 1= nej inte kroppsligt aktivt alls, 2=ja, lite kroppsligt aktivt, 3=Ja måttligt kroppsligt aktivt, 4= Ja, mycket kroppsligt aktivt, 5= annat) The answers will be dichotomized with a cut-off point between 2 and 3 prior to analysis.*

Q 205: Hur ofta har Du varit fysiskt aktivt i 30 minuter eller mer den senaste månaden..? *With a 4 point Likert scale (1= aldrig, 2=ibland (1-2 ggr/v), 3=Ofta (3-4 ggr/v), 4= Dagligen eller nästan dagligen (5-7 ggr/vecka)) The answers will be dichotomized with a cut-off point between 2 and 3 prior to analysis.*

Q 221: Hur ofta har Du varit tvungen att trycka på eller krysta för att börja kissa den senaste månaden? *With a 6 point Likert scale (1=aldrig, 2=färre än 1 av 5 vattenkastningar, 3=färre än hälften av vattenkastningar, 4= ungefär hälften av vattenkastningar, 5= fler än hälften av vattenkastningar, 6=alltid). The answers will be dichotomized with a cut-off point between 3 and 4 prior to analysis.*

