### **Questionnaire 12 months**

Q 12: Har ditt arbete varit kroppsligt aktivt den senaste månaden? *With a 6 point Likert scale (0=Inte aktuellt jag jobbar inte, 1= nej inte kroppsligt aktivt alls, 2=ja, lite kroppsligt aktivt, 3=Ja*

[figure not shown]

*måttligt kroppsligt aktivt, 4= Ja, mycket kroppsligt aktivt, 5= annat) The answers will be dichotomized with a cut-off point between 2 and 3 prior to analysis.*

*Q 219: Hur ofta har Du varit fysiskt aktivt i 30 minuter eller mer den senaste månaden..? With a 4 point Likert scale (1= aldrig, 2=ibland (1-2 ggr/v), 3=Ofta (3-4 ggr/v), 4= Dagligen eller nästan dagligen (5-7 ggr/vecka)) The answers will be dichotomized with a cut-off point between 2 and 3 prior to analysis.*

*Q 235: Hur ofta har Du varit tvungen att trycka på eller krysta för att börja kissa den senaste månaden? with a 6 point Likert scale (1=aldrig, 2=färre än 1 av 5 vattenkastningar, 3=färre än hälften av vattenkastningar, 4= ungefär hälften av vattenkastningar, 5= fler än hälften av vattenkastningar, 6=alltid). The answers will be dichotomized with a cut-off point between 3 and 4 prior to analysis. Interpreted as risk factor and included in analyses if answered "yes" on same or previous questionnaire as inguinal hernia is identified.*

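### Postoperative straining to void is declared a risk factor included in the analyses, but the factor list, the covariate rule and the model statement leave it out, so the candidate set for the primary model contradicts itself

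*SAP*

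**What the plan says.** **Where straining is coded.** The part of the SAP's Variables and Endpoints section that gives the sources of baseline characteristics, tumour factors, comorbidities and risk factors words the straining question and cuts it between categories 3 and 4 on four questionnaires:
- preoperative: "Q 146: Hur ofta har Du varit tvungen att trycka på eller krysta för att börja kissa den senaste månaden"
- three months: "Q 221: Hur ofta har Du varit tvungen att trycka på eller krysta för att börja kissa den senaste månaden"
- 12 months: Q 235
- 24 months: Q 256

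**Where it is said to be used.** Only the 12- and 24-month items carry a statement of use: "Interpreted as risk factor and included in analyses if answered" yes on the same questionnaire as the one where the hernia is identified, or on a previous one. The 24-month entry gives the rule twice.

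**Where it is missing.** The numbered list of risk factors to be evaluated has nine entries, none urinary. The Statistical method section names "possible risk factors (age, physical workload, BMI, diabetes, pulmonary disease, smoking, hernia prior operation, physical activity and tumour size", again nine and none urinary. The section on covariates, stratum and subgroups closes the set: "No additional variables apart from the variables that will be evaluated for risk factors will be included as covariates in the statistical model".

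**Baseline source.** The summary line of preoperative items ends with "physical activity (Q143), urinary flow (Q149"). Q149 is not worded or coded anywhere in the SAP. Q 146, which is worded and coded just below, does not appear in that line.

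**The concern.** One part of the SAP puts postoperative straining into the analyses and three other parts leave no room for it. This would be a small editorial matter if the risk-factor analysis stood apart from the primary comparison. It does not: the Statistical method section estimates the technique effect and the risk factors in a single modified Poisson model, with covariates chosen by purposeful selection. A selection algorithm needs a fixed list of candidates. Here an analyst could defend nine or ten after seeing the data, and the adjusted RALP versus RRP relative risk may depend on that choice.

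The route into the model is also a poor one. The 12- and 24-month answers come after surgery, so they may themselves be affected by the technique. The rule then defines exposure by reference to the questionnaire on which the hernia was found. A man without a hernia has no such questionnaire, and the SAP does not say how he is coded.

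For the secondary objective, following the list and the model statement means that a variable the SAP calls a risk factor receives no estimate.

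**Working it through.** **1. Passages side by side.**

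| Place in SAP | Straining in the model? |
|---|---|
| Preoperative questionnaire, Q 146 | Worded and cut; no statement of use |
| Three months, Q 221 | Worded and cut; no statement of use |
| 12 months, Q 235 | Yes, by the timing rule |
| 24 months, Q 256 | Yes, by the same rule |
| Numbered risk-factor list | No (nine factors) |
| Covariates, stratum and subgroups | Only evaluated risk factors allowed |
| Statistical method | No (nine factors) |

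The candidate count is 9 by the list and the model statement, and 9 + 1 = 10 by the 12- and 24-month rule.

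**2. Is it just a descriptive variable?** Smoking, physical activity and workload also have stated codings, and all three are among the nine. Straining is coded in the same way, but is neither among the nine nor among the variables to be summarised under Demography and patient characteristics. Its coding therefore serves no named purpose unless it is modelled.

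**3. Does the word preoperative in the list's title explain the omission?** Not fully. Physical workload is on that list, yet its coded items come only from the 3-, 12- and 24-month questionnaires. Straining does have a coded preoperative item.

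**4. Plan's own figures.** The SAP gives no prevalence of straining and no hernia risk ratio for it, so there is no figure to reproduce on this point. Its power statements (35% and 55%) do not depend on it.

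**5. Possible effect of omission on the primary ratio.** All inputs here are assumptions: prevalence of preoperative straining 20% in one arm and 25–30% in the other, and a hernia risk ratio of 1.5. The factor by which omission multiplies the RALP:RRP ratio is

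(1 + p_RALP × 0.5) / (1 + p_RRP × 0.5)

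- RALP 20%, RRP 25%: 1.10 / 1.125 = 0.978
- RALP 20%, RRP 30%: 1.10 / 1.15 = 0.957
- equal prevalence: 1.00
- RALP 25%, RRP 20%: 1.125 / 1.10 = 1.023
- RALP 30%, RRP 20%: 1.15 / 1.10 = 1.045

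The range is about 0.96 to 1.05. As a yardstick, the previous study cited under Sample size gives 6% / 7.5% = 0.80. On the log scale, 0.978 and 0.957 are 10% and 20% of ln(0.80), and the reversed cases are the same size in the other direction.

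**6. Why the missing rule for men without hernia matters.** Assume that straining has no true association with hernia, has prevalence q at each of four questionnaires independently, and that hernia risk is 10.5%. Suppose cases are coded from two questionnaires (the one where the hernia is found and the one before it) and non-cases from all four. The exposed share is then 1 − (1 − q)² in cases and 1 − (1 − q)⁴ in non-cases.

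For q = 5% these are 0.0975 and 0.1855. The hernia risk is:
- in strainers: 0.105 × 0.0975 / (0.105 × 0.0975 + 0.895 × 0.1855) = 0.058
- in the others: 0.105 × 0.9025 / (0.105 × 0.9025 + 0.895 × 0.8145) = 0.115

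The ratio is 0.51 where the truth is 1. For q = 3% and 10% it is 0.51 and 0.48. This is one possible coding, not one the SAP states. It concerns the straining coefficient, not the RALP versus RRP ratio.

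**The case against.** The strongest defence is that the two operative statements, the numbered list and the model, agree: nine factors and no urinary item. The covariates section supports them. Against this stands one coding note, repeated, which may be left over from an earlier idea. The section that holds the straining items also holds sociodemographics, previous abdominal surgery, ASA class, PSA and Gleason score, none of which is among the nine, so being defined there does not mean being modelled. Purposeful selection may also drop a listed candidate, so listing straining would not by itself settle the adjusted estimate.

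Much of this stands, and it limits the point in three ways.
- A reader might infer that the SAP puts **baseline** straining in the model. It does not say so: the statement of use belongs to Q 235 and Q 256, while Q 146 and Q 221 are only worded and cut.
- A reader might infer that the baseline item has two conflicting numbers. "urinary flow (Q149") may be a different question from Q 146, and the questionnaire is not at hand to decide.
- A reader might infer that the omission biases the comparison in favour of RALP. That requires more straining among RRP men, for which the SAP gives no evidence.

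The defence does not remove the conflict. The 12- and 24-month sections say in terms that the variable is included in the analyses, and nothing in the SAP withdraws that.

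**Conclusion.** The contradiction holds, for the postoperative items. The 12- and 24-month sections include straining, while the risk-factor list, the covariate rule and the model statement exclude it. The conflict reaches the primary analysis because a single model serves both objectives. Following the 12- and 24-month rule would be the worse outcome, since it brings in a covariate measured after surgery and defined by the timing of the event.

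The preoperative part is narrower: Q149 is cited without coding, and Q 146 is coded without being cited.

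The size and direction of any bias in the RALP versus RRP ratio are unknown. The range of about 0.96 to 1.05, with 1.00 at equal prevalence, rests wholly on the assumed prevalences and risk ratio and shows only that the effect could be modest in either direction. The conclusion that the text must be reconciled does not depend on those assumptions.

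**What to change.** 1. In the 12- and 24-month questionnaire sections, delete the rule that includes straining in the analyses, and state that postoperative straining does not enter the RALP versus RRP model.
2. Choose one of two options and state it: (a) add preoperative straining (Q 146, cut between 3 and 4, coded the same way for all men whatever their outcome) as a tenth candidate in both the numbered list and the Statistical method section; or (b) state that straining is not a candidate. Either removes the contradiction. Under (a), the item precedes surgery and does not depend on the outcome.
3. Check Q149 against the questionnaire, then correct the number or give the item a coding and a purpose. Cite Q 146 in the summary line if it is used.

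The cost is SAP wording and at most one extra model term, from data already collected.

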### **Questionnaire three months:**

Q 8: Har ditt arbete varit kroppsligt aktivt den senaste månaden? *With a 6 point Likert scale (0=Inte aktuellt jag jobbar inte, 1= nej inte kroppsligt aktivt alls, 2=ja, lite kroppsligt aktivt, 3=Ja måttligt kroppsligt aktivt, 4= Ja, mycket kroppsligt aktivt, 5= annat) The answers will be dichotomized with a cut-off point between 2 and 3 prior to analysis.*

Q 205: Hur ofta har Du varit fysiskt aktivt i 30 minuter eller mer den senaste månaden..? *With a 4 point Likert scale (1= aldrig, 2=ibland (1-2 ggr/v), 3=Ofta (3-4 ggr/v), 4= Dagligen eller nästan dagligen (5-7 ggr/vecka)) The answers will be dichotomized with a cut-off point between 2 and 3 prior to analysis.*

Q 221: Hur ofta har Du varit tvungen att trycka på eller krysta för att börja kissa den senaste månaden? *With a 6 point Likert scale (1=aldrig, 2=färre än 1 av 5 vattenkastningar, 3=färre än hälften av vattenkastningar, 4= ungefär hälften av vattenkastningar, 5= fler än hälften av vattenkastningar, 6=alltid). The answers will be dichotomized with a cut-off point between 3 and 4 prior to analysis.*

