### **Questionnaire 24 months**

*Q 23: Har ditt arbete varit kroppsligt aktivt den senaste månaden? With a 6 point Likert scale (0=Inte aktuellt jag jobbar inte, 1= nej inte kroppsligt aktivt alls, 2=ja, lite kroppsligt aktivt, 3=Ja måttligt kroppsligt aktivt, 4= Ja, mycket kroppsligt aktivt, 5= annat) The answers will be dichotomized with a cut-off point between 2 and 3 prior to analysis.*

*Q 230: Hur ofta har Du varit fysiskt aktivt i 30 minuter eller mer den senaste månaden..? With a 4 point Likert scale (1= aldrig, 2=ibland (1-2 ggr/v), 3=Ofta (3-4 ggr/v), 4= Dagligen eller nästan dagligen (5-7 ggr/vecka)) The answers will be dichotomized with a cut-off point between 2 and 3 prior to analysis.*

*Q 256: Hur ofta har Du varit tvungen att trycka på eller krysta för att börja kissa den senaste månaden? With a 6 point Likert scale (1=aldrig, 2=färre än 1 av 5 vattenkastningar, 3=färre än hälften av vattenkastningar, 4= ungefär hälften av vattenkastningar, 5= fler än hälften av vattenkastningar, 6=alltid). The answers will be dichotomized with a cut-off point between 3 and 4 prior to analysis. Interpreted as risk factor if answered "yes" on same or previous questionnaire as inguinal hernia is identified. Interpreted as risk factor and included in analyses if answered "yes" on same or previous questionnaire as inguinal hernia is identified*

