## **HANDLING OF MISSING VALUES AND OTHER DATA CONVENTIONS**

In order to handle the issue with missing data of risk factors used in the model, multiple imputation by means of chained equations (MICE) will be used.

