#### **Demography and patient characteristics**

The following variables will be summarized and described:

- Age (median (Q1 ; Q3))
- BMI (median (Q1 ; Q3))
- Diabetes yes/no
- Cardiopulmonary disease Yes/no
- Smoking/non-smoking
- Heavy work load yes /no
- Tumour stage: low risk, and high risk
- Physical activity in history

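### Read literally, the workload cut-off counts the answer 'annat' (other, code 5) as physically active work at all three follow-up questionnaires

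*SAP*

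**What the plan says.** Under Variables and Endpoints, the three-month questionnaire section defines the workload item Q 8. The lower codes are given as "With a 6 point Likert scale (0=Inte aktuellt jag jobbar inte, 1= nej inte kroppsligt aktivt alls, 2=ja, lite kroppsligt aktivt". Code 3 is moderately active. The top of the scale and the rule are "4= Ja, mycket kroppsligt aktivt, 5= annat) The answers will be dichotomized with a cut-off point between 2 and 3 prior to analysis".

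The 12-month section repeats this for Q 12 ("måttligt kroppsligt aktivt, 4= Ja, mycket kroppsligt aktivt, 5= annat) The answers will be dichotomized with a cut-off point between 2 and 3") and the 24-month section for Q 23 ("5= annat) The answers will be dichotomized with a cut-off point between 2 and 3 prior to analysis"). None of the three makes an exception for code 5 or code 0.

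The variable is used in two places. Demography and patient characteristics lists it as "Heavy work load yes /no". Statistical method makes it a candidate in the modified Poisson model: "possible risk factors (age, physical workload, BMI, diabetes, pulmonary disease, smoking, hernia prior operation, physical activity and tumour size) will be evaluated". For risk factors with missing data, the section on missing values says only that "multiple imputation by means of chained equations (MICE) will be used".

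**The concern.** The item is called a six-point Likert scale, but only codes 1 to 4 run in order of intensity. Code 0 means not working and code 5 means other. A single numerical cut suits an ordered scale. Here it sends code 5 to the upper group merely because 5 is greater than 2.

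The other items dichotomised in the same sections do not have this problem. Physical activity (Q 143, 205, 219, 230) and straining to urinate (Q 146, 221, 235, 256) are ordered from end to end, so one cut is enough. Workload gets the same kind of rule although its end codes are not ordinal.

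At stake is the meaning of the exposed group. It would contain men whose workload is not known, which can shift the estimated association and influence whether the purposeful-selection procedure keeps the variable. The same men would be described as having heavy work in Table 1 if that table uses the same coding.

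**Working it through.** **Step 1: apply the rule as written.** Codes above 2 form the upper group and the rest the lower group:

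- upper: 3 (moderately active), 4 (very active), 5 (other)
- lower: 0 (not working), 1 (not at all active), 2 (a little active)

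The result is the same for Q 8, Q 12 and Q 23.

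**Step 2: look for a repair elsewhere in the SAP.** Multiple imputation applies to missing risk-factor data. 'Other' is a recorded answer that the cut assigns to a group, so it would not be imputed. The section on covariates, stratum and subgroups adds no coding convention. The demography list gives the label but no codes. Nothing removes code 5 from the upper group.

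**Step 3: illustrate the size.** The SAP has no figure to reproduce here; every input below is an assumption:

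- h = share with codes 3-4: 15% or 30%
- q = share answering 'other': 1% to 10%
- R = true relative risk of codes 3-4 against the lower group: 1.5
- f = fraction of 'other' who in fact do active work: 0, 0.5 or 1; the remainder are at baseline risk

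Formula: observed RR = [h·R + q·(f·R + 1 − f)] / (h + q).

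With h = 15% and f = 0:

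- q = 1%: (0.225 + 0.01) / 0.16 = 1.47
- q = 5%: (0.225 + 0.05) / 0.20 = 1.38
- q = 10%: (0.225 + 0.10) / 0.25 = 1.30

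| h | f | q = 1% | q = 5% | q = 10% |
|---|---|---|---|---|
| 15% | 0 | 1.47 | 1.38 | 1.30 |
| 15% | 0.5 | 1.48 | 1.44 | 1.40 |
| 15% | 1 | 1.50 | 1.50 | 1.50 |
| 30% | 0 | 1.48 | 1.43 | 1.38 |

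The share of the upper group that consists of 'other' is q / (h + q). At h = 15% this is 0.01/0.16 = 6%, 0.05/0.20 = 25% and 0.10/0.25 = 40%.

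**Step 4: what decides the direction.** The estimate falls when the hernia risk among 'other' is below that of codes 3-4, is unchanged when the two are equal, and rises when it is above. The workload item is listed only in the postoperative questionnaires, in the same period in which hernias are reported. Error unrelated to the outcome therefore cannot be taken for granted.

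**Step 5: after the change.** With code 5 out of the upper group, codes 3-4 against 0-2 return R in this model, provided that answering 'other' carries no further information on risk.

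**The case against.** The strongest reply is that the SAP never says that 'other' counts as heavy work. It gives a cut on what it takes to be a Likert scale and is silent on the non-ordinal codes, and a sensible analyst might set code 5 aside. That is possible, but the rule is explicit, appears three times without exception, and followed literally puts code 5 in the upper group. The text needs correcting even if the intention was sound.

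A reader might go further and infer that the rule certainly dilutes the workload effect. The SAP does not support that. It gives neither the share answering 'other', nor the share in codes 3-4, nor the risk in either group. The f = 0 rows take every 'other' man to be at baseline risk; if all do active work there is no dilution. Because the question is asked after surgery, bias in the other direction cannot be excluded.

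A reader might also regard pooling code 0 with light work as a second error. It is not. The reported variable is heavy work load yes or no, and a man who does not work has no heavy work load. Age, which might be mixed up with not working, is itself a candidate in the model, although selection could drop it.

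On weight, workload is one of nine candidate risk factors, and the section on interpretation already promises caution about associations. This stands and limits the importance of the point. It does not make the classification correct.

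**Conclusion.** The point holds as a coding error in a stated rule: read literally, the cut places an answer of unknown intensity with moderately and very active work at all three time points, and no other section corrects it. This rests on the text alone.

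Attenuation of the workload association is likely, but neither its size nor its direction can be derived from the SAP. Under the assumptions shown (15% in codes 3-4, true relative risk 1.5, 'other' at baseline risk), the loss runs from slight at 1% 'other' to moderate at 10%. It disappears if those men do active work.

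The effect falls on the secondary objective of evaluating risk factors. It would be too strong to conclude that the RALP versus RRP comparison is biased: that estimate is reached only through adjustment, and only if workload is retained in the model.

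**What to change.** For Q 8, Q 12 and Q 23, replace the bare cut-off with an explicit list of codes. The upper group is codes 3 and 4 only. Code 5 is taken out of it, by one of two rules to be chosen before analysis:

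- set it to missing and handle it under the existing multiple imputation plan, which assumes that these men resemble other respondents given the covariates; or
- keep it as a separate category, which avoids that assumption at the price of one more, possibly small, group.

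Code 0 may stay in the lower group. Use the same coding for the workload row in Table 1.

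The cost is a sentence or so in each of the three questionnaire sections and a simple recode, with no new data. The change does not settle which of the three postoperative answers, or what combination of them, enters the model, although the SAP lists workload among preoperative risk factors. That choice can be written down in the same edit.
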